**Mental Illness not related to ICU presentation**

Where a patient has a pre-existing mental illness which is already being managed by their GP or other service, no further intervention will be provided.

Where a new mental illness is identified or suspected, but unrelated to their ICU admission, contact details for relevant services will be provided to the participant and the psychiatrist will notify the patient’s GP of the diagnosis and advise referral for ongoing review and treatment as indicated.

**Intervention Follow-up**

The Psychiatrist will follow-up all patients where an intervention is initiated 4-6 weeks after their appointment. If there has been least partial clinical response, a letter will be sent to the participant’s GP recommending continuing current cares with ongoing monitoring. If there has been no response or a non-urgent deterioration, a letter will be sent to the GP suggesting referral for ongoing psychiatric review.

**Imminent risks**

If at clinic assessment the participant appears to require inpatient psychiatric treatment, or there is concern of an imminent risk such as (suicidal ideation with intent and plan), or an urgent clinical deterioration, the participant will be directed to the Redcliffe Emergency Department for immediate review by their local mental health service.

If the imminent risk is identified during the intervention follow-up, the participant will be encouraged to attend their local hospital for urgent review by the mental health service.

## 6 Month Outcomes Follow-up

At the completion of data collection at the clinic appointment, permission will be sought to contact participants again 6 months after their appointment and participants will be asked to nominate a preferred form of contact.

A member of the research team will contact the participant via their preferred contact method approximately 6 months after their clinic appointment.

After providing consent to continue participating, the participant will complete the outcome measure bundle again.

## Data management and security:

All data will be treated in confidence and only made accessible to members of the research team on an as needs basis. All paper records will be stored in a locked filing cabinet, and any electronic databases will be stored on password protected computers. For dissemination of results, participants will only be referred to in the coded form e.g. “Participant A”, “Participant B” etc. All records will be destroyed (permanently deleted or shredded as appropriate) after 15 years, as per ‘Good Clinical Practice’ (GCP) guidelines.

Electronically collected data will be directly entered into REDCap, hosted on a Queensland Health server. Hard copy responses will be manually entered into REDCap by a member of the research team. Once recruitment is complete, Data will be cleaned and uploaded to statistical software package R for analysis.

## Statistical analysis

The demographics and results of the Baseline Outcome Measures Bundle will be described using proportions and associated 95% confidence intervals and compared between intervention and control groups to check the integrity of the randomisation.

Responses to the Post Appointment Questionnaire will be assumed to be additive and averaged to produce the primary outcome measure. Differences between groups will be assessed using t-test.

Changes in secondary outcome measures between baseline and 6 months will be compared between intervention and control groups to identify any clinically and statistically significant differences using ANCOVA regression with patients results at baseline fitted as a covariate. The model residuals will be checked to look for outliers and bi-modality. Leave-one-out sensitivity analyses will be used to look for patients that strongly influence the results.

Two-by-two tables will be created of the predicted and observed PICS, together with statistics on sensitivity, specificity, and negative and positive predictive value. Models will be checked for influential observations and outliers. The results will be reported using the EQUATOR TRIPOD checklist to ensure completeness and transparency[29].

The overall characteristics of the sample will be described using summary statistics. This will help inform the generalisability of our results. The number of patients approached and consented will be tabulated, together with the number who dropped out or died.

.

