# Aims and objectives

The primary objective of this pilot RCT study is to:

1. To evaluate feasibility (cost and practicability) and acceptability of an early psychiatric intervention in a post-ICU clinic.

Secondary Objectives are:

1. Assess the impact of early psychiatric assessment and provision of referral options on self-efficacy and rates of health service access for patients requiring psychological intervention post-ICU
2. Measure the change in symptom severity for anxiety, depression, and PTSD between presentation, and 6 months after presentation.
3. Measure the impact on work, income, and independence in activities of daily living (ADL)

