## Sampling and recruitment

Patients attending the Redcliffe Post-ICU clinic will be informed about the trial of an inclusion of an early psychiatric review as part of the clinic following their completion of standard clinic cares (see Appendix 1 for the Standard Operating Procedures).

If the patient expresses interest in the study, they will be provided written and verbal information regarding the purpose and aims of the study and invited to ask any questions they have about the study before being invited to participate. Potential participants will not be aware if they have been randomised to the control or intervention arm at this stage.

The potential participant will be provided multiple opportunities to discuss the study with members of staff not involved in the study. Information will be provided in writing and verbally before the patient is invited to consent to participate in the study.

A patient information and consent form will be provided. People who agree to participate will complete the written consent form before any data collection takes place. Patients who consent to participate will be randomised using a simple randomisation schedule. Participants randomised to the intervention arm will be offered an appointment with the psychiatrist in addition to standard clinic cares, whereas participants randomised to the control arm will receive standard clinic cares only.

For those attending their appointment over the phone, verbal consent will be obtained and witnessed. People who give consent will give permission for research staff to access data from their clinical records and will complete a series of questionnaires examining their premorbid function, experiences in ICU and their subsequent recovery across a range of domains.

To monitor recruitment, a re-identifiable log will be kept that will document patients eligible for approach, and subsequent contact.

Participants will be able to withdraw from the study at any time. If a participant that has been randomised to receive the early psychiatric intervention chooses to withdraw consent, they will receive the standard cares provided by the clinic without the intervention, and any collected data will be withdrawn from the study.

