## Post Appointment Questionnaire

To address the primary outcome, the **Post Appointment Questionnaire** is an 8 item self-reported acceptability measure that has been specifically developed for this study. It has been adapted from similar surveys used in previous acceptability studies. Questions focus on whether the participant found their appointment helpful, how confident they feel about managing any psychological symptoms they have or may develop, and how optimistic they feel about their recovery.

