## Follow-up Survey

At the 6-month timepoint, participants will repeat the Post Appointment Questionnaire, PICS Measures (including HADS and EQ5D-5L), Life Events Checklist, Generalised Self Efficacy Screen and Patient Employment Information Questionnaire, as well as the Health Services Use Questionnaire described below. The follow-up Survey can be found in Appendix 3.

This **Health Services Use** Questionnaire has 11-items and been adapted from a questionnaire utilised in a recent injury vulnerability study[26]. It explores how often the participant has attended a range of clinical, allied health and alternative health services, whether these services were helpful for their mental health, and for those think they needed more help from health professionals than was accessed, the main reason they didn’t get this help.

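### The single primary outcome and its between-arm t-test leave cost and practicability unaddressed and do not estimate how acceptable the psychiatric intervention is to those offered it

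*Protocol*

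**What the plan says.** The primary objective (Protocol, Aims and objectives) is "To evaluate feasibility (cost and practicability) and acceptability of an early psychiatric intervention in a post-ICU clinic".

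The Post Appointment Questionnaire section presents that instrument as the means of addressing the primary outcome. It "is an 8 item self-reported acceptability measure that has been specifically developed for this study". On content: "Questions focus on whether the participant found their appointment helpful, how confident they feel about managing any psychological symptoms they have or may develop", and the same sentence adds optimism about recovery.

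The Statistical analysis section then states: "Responses to the Post Appointment Questionnaire will be assumed to be additive and averaged to produce the primary outcome measure". The comparison follows: "Differences between groups will be assessed using t-test".

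Under Sampling and recruitment, the intervention arm is offered a psychiatrist appointment on top of usual clinic care, while "participants randomised to the control arm will receive standard clinic cares only". At six months, "participants will repeat the Post Appointment Questionnaire" (Follow-up Survey).

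Two statements bear on feasibility outside the primary outcome. The Statistical analysis section will tabulate how many patients were approached, consented, dropped out or died. Sampling and recruitment provides for a log of patients eligible for approach and later contact.

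**The concern.** The objective has three parts (cost, practicability, acceptability), and the plan gives one primary result, a difference in mean questionnaire score between arms. Two of the three parts have no link to that result. The third is approached through a contrast between two kinds of visit, because controls never meet the psychiatrist.

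Under Dissemination and outcome, the results are meant to inform future studies and further development of a targeted intervention. A reader planning such a study needs to know what the intervention costs to deliver, whether patients take it up and stay, and how those who received it rated it. Followed exactly, the plan puts none of these at the head of its results and does not collect the first. Staff time that is not recorded as it is spent is hard to recover later.

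**Working it through.** **1. Objective against what is measured**

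| Part of primary objective | What the Protocol provides | Tied to the primary outcome? |
| --- | --- | --- |
| Cost | No measure of psychiatrist time or delivery cost is described. Health Services Use covers patients' attendance at services; the employment questionnaire covers their work and income. | No |
| Practicability | Counts approached, consented, dropped out, died; recruitment log. Uptake of the psychiatrist appointment is not named. | No |
| Acceptability | Averaged 8-item questionnaire, arms compared by t-test | Yes, as a between-arm difference |

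The Resources section says the study runs on in-kind contributions from the investigators, with Psychiatry represented in the team. Study spending would therefore not reveal the delivery cost either.

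**2. What the t-test estimates**

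Let m_I be the mean score after the clinic visit with a psychiatrist, and m_C the mean after the standard visit. The test concerns m_I − m_C. Acceptability to those offered the intervention concerns m_I. If both visits are rated equally well, the difference is zero although the intervention is well liked. If both are rated poorly but unequally, the difference can be non-zero although neither is liked. The sign and significance of the difference therefore do not fix m_I.

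**3. Precision of the planned comparison**

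Inputs: 15 per arm (Participants and sample calculation) and 1:1 allocation (Study procedure). Assumption: two-sided 5% level, as none is stated. Results are in SD units because the questionnaire's SD is not given. The Protocol gives no power or precision figure to reproduce.

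Half-width of the 95% interval for the difference = t(0.975; 28) × √(2/15) = 2.048 × 0.365 = 0.75 SD.

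An observed difference of exactly zero would thus be compatible with true differences from −0.75 to +0.75 SD. By the noncentral t distribution, 80% power requires a difference of 1.06 SD; power at 0.5 SD is 26%. With 12 evaluable per arm (assumed), the half-width is 2.074 × √(2/12) = 0.85 SD.

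**4. Precision of the quantities that match the objective**

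- Intervention-arm mean, n = 15: t(0.975; 14)/√15 = 2.145/3.873 = 0.55 SD half-width. With 12 evaluable it is 0.64 SD.
- Uptake (assumed counts, exact intervals): 12/15 gives 80% (52% to 96%); 15/15 gives 100% (78% to 100%).
- Retention (assumed count): 24/30 gives 80% (61% to 92%).

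These are also imprecise. Their advantage is that each estimates something the objective names.

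**The case against.** The strongest reply is that the comparison suits an add-on. Intervention participants receive usual clinic care and the psychiatrist, and the questionnaire asks about their appointment. Their rating alone cannot separate the two components; the control arm supplies the reference, so the difference estimates what the psychiatrist adds. The analysis also yields the intervention-arm mean as a by-product. This stands: the between-arm estimate should be kept, and a reader who infers that it is invalid or useless for acceptability goes too far.

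Second, a reader might infer that feasibility would have no result at all. The planned table of patients approached, consented and lost, and the recruitment log, contradict that. What remains is that these counts are not tied to the primary objective, and uptake is missing.

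Third, a reader might object to averaging helpfulness with confidence and optimism, on the ground that these belong with self-efficacy. The eight items are not in the text at hand, only a summary of their focus, and self-efficacy has its own scale. The documents do not settle that point.

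Fourth, the power figures refute nothing. The Protocol calls the trial a pilot, claims no power, and sets no rule that a non-significant test means the intervention is unacceptable. The figures only limit what a null result can mean. Nor does 30 of about 80 clinic patients a year (37.5%) give a required consent rate, because the 80 are all patients reviewed, not eligible patients approached.

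Fifth, progression limits and explicit naming of the primary time point are details that a statistical analysis plan may supply. The natural reading is already that the first administration is the main one. Delivery cost is different: an analysis plan cannot analyse data that nobody collects.

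**Conclusion.** The point holds as a mismatch between the primary objective and the primary outcome with its test. It is firmest for cost: the Protocol names it in the primary objective and describes no measure of it. For practicability, relevant counts exist but stand apart from the objective, and uptake is not named. For acceptability, the planned test answers a narrower question, whether adding the psychiatrist changes the rating of the visit, to within about ±0.75 SD at full recruitment.

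The size rests on 15 evaluable patients per arm and a two-sided 5% level, the latter assumed. The statement on cost rests on the Protocol text; the survey appendices are not at hand, but the text describes them as patient questionnaires. The documents do not support concluding that the trial yields no feasibility information or that the between-arm comparison is wrong in itself.

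**What to change.** 1. **Cost.** Log psychiatrist minutes per intervention participant (visit, letters, 4-6 week follow-up) in REDCap, which the study already uses. Cost per participant = minutes/60 × hourly salary rate, with the rate and its source stated. Start the log before the first participant is seen.
2. **Practicability.** Name the existing approach, consent and retention counts, plus uptake of the psychiatrist appointment, as primary feasibility outcomes with exact 95% confidence intervals. Count retention over everyone randomised: the exclusion of consenters without baseline or 6-month data would, taken literally, make retention complete by construction.
3. **Acceptability.** Make the intervention-arm questionnaire score at the administration straight after the appointment, with its 95% confidence interval, the primary acceptability result. Keep the between-arm difference with its interval as a supporting estimate of the add-on's incremental effect.

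This costs a change of Protocol wording, a REDCap field and a few minutes of logging per patient. The drawback is that an intervention-arm rating cannot by itself separate the psychiatrist from usual clinic care, which is why the between-arm difference stays.

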### Background information

The following questionnaires have been selected to provide information on the patient’s premorbid risk/protective factors and baseline level of function.

The “Metro North Patient Experience Survey – outpatient and community” is an 11-question patient reported experience measure (**PREM**) and will be used to collect information about the participant’s experience during their ICU admission.

The Life Events Checklist (**LEC**) for DSM-5 is a self-report measure designed to screen for potentially traumatic events in a respondent's lifetime. The LEC-5 assesses exposure to 16 events known to potentially result in PTSD or distress and includes one additional item assessing any other extraordinarily stressful event not captured in the first 16 items[20]. There is no formal scoring protocol or interpretation per se, other than identifying whether a person has experienced one or more of the events listed. Respondents indicate varying levels of exposure to each type of potentially traumatic event included on a 6-point nominal scale, and respondents may endorse multiple levels of exposure to the same trauma type. The LEC-5 does not yield a total score or composite score.

The Posttraumatic Adjustment Screen (**PAS**) is a 10-item screening index that has been designed to facilitate the early identification of individuals most at risk for developing PTSD and/or depression following a traumatic injury.

The **General Self Efficacy Scale** is a 10-item psychometric scale that is designed to assess optimistic self-beliefs to cope with a variety of difficult demands in life[21].

The **Patient Employment Information Questionnaire** has been amended from a Questionnaire previously used in epilepsy research and reworded to relate to the patient’s ICU admission. It consists of seven questions around changes to employment and income since their ICU admission.

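### The primary t-test leaves out the baseline self-efficacy score that the trial already collects, which gives up precision and leaves the single-trial estimate open to chance imbalance

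*Protocol*

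**What the plan says.** The Statistical analysis section of the protocol defines the primary outcome and its test in two sentences: "Responses to the Post Appointment Questionnaire will be assumed to be additive and averaged to produce the primary outcome measure", and "Differences between groups will be assessed using t-test". No covariate is named.

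Under Post Appointment Questionnaire, the instrument "is an 8 item self-reported acceptability measure that has been specifically developed for this study". Its items ask about the helpfulness of the appointment and also "how confident they feel about managing any psychological symptoms they have or may develop, and how optimistic they feel about their recovery". It is not among the Initial Survey instruments. It is given after the appointment and again at 6 months, so it has no pre-appointment value.

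The Initial Survey includes the General Self Efficacy Scale, which "is a 10-item psychometric scale that is designed to assess optimistic self-beliefs to cope with a variety of difficult demands in life". The intervention section has the psychiatrist review the baseline questionnaires before meeting the participant, so the scale is available before the intervention starts.

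For the secondary outcomes, the same Statistical analysis section prescribes ANCOVA with the baseline value as covariate. It also compares baseline measures between the arms, but attaches no consequence to what that comparison shows.

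**The concern.** Confidence in handling symptoms and optimism about recovery are likely to depend partly on how the patient felt before the clinic visit. A patient with strong coping beliefs will tend to score higher on those items in either arm. With about 15 patients per arm and no stated stratification, the arms can differ noticeably in such a trait by chance, and the unadjusted difference carries part of that imbalance.

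A baseline measure of a closely related trait is already in the data set. Leaving it out gives a wider interval than necessary if the two scores are at least moderately correlated. It also leaves the team without a prespecified response if the planned baseline comparison shows the arms to differ in self-efficacy, and an adjustment chosen after seeing that difference would look data-driven.

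**Working it through.** The protocol gives no SD, effect size, alpha or power, so there is no stated figure to reproduce. Everything below is in SD units of the relevant score.

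**Inputs**
- n = 15 per arm (Participants and sample calculation).
- 1:1 allocation, no stratification stated (Study procedure).
- Two-sided alpha of 0.05 (assumed).
- Correlation ρ between baseline General Self Efficacy and the questionnaire average: not given; assumed 0.3, 0.5 or 0.7.

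**1. Chance imbalance at baseline**
- SD of the difference in arm means = √(2/15) = 0.365.
- 95% range: ±1.96 × 0.365 = ±0.72 SD.
- Probability that the imbalance exceeds 0.5 SD in either direction: 2 × [1 − Φ(0.5/0.365)] = 0.17.

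**2. Effect of an imbalance on the unadjusted estimate**
- Expected shift = ρ × imbalance. For 0.5 SD: 0.15, 0.25 or 0.35 SD.

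**3. Long-run behaviour** (100,000 simulated null trials for each ρ)
- The t-test has a mean difference of 0.00 and rejects in 4.9% to 5.0% of trials. ANCOVA rejects in 4.8% to 5.0%.
- In the roughly 17% of trials with an imbalance above 0.5 SD, the t-test rejects in 7%, 11% or 18% (ρ = 0.3, 0.5, 0.7), and ANCOVA in about 5%.

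**4. Precision**
- Unadjusted half-width = t(0.975; 28) × 0.365 = 2.048 × 0.365 = 0.748.
- Adjusted half-width = t(0.975; 27) × 0.365 × √(1 − ρ²), with t = 2.052.

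| ρ | √(1 − ρ²) | SE | Half-width | Difference detectable with 80% power |
|---|---|---|---|---|
| unadjusted | 1 | 0.365 | 0.748 | 1.06 |
| 0.3 | 0.954 | 0.348 | 0.715 | 1.01 |
| 0.5 | 0.866 | 0.316 | 0.649 | 0.92 |
| 0.7 | 0.714 | 0.261 | 0.535 | 0.76 |

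**5. Where adjustment stops paying**
- The table ignores the small penalty for estimating the slope. For a normally distributed covariate, that penalty multiplies the variance on average by 1 + 1/(30 − 4) = 1.038, so the half-width by 1.019.
- With the change in t (2.052/2.048 = 1.002), the total penalty is 1.019 × 1.002 ≈ 1.021, or about 2% at ρ = 0.
- Break-even: √(1 − ρ²) = 1/1.021, which gives ρ ≈ 0.20.
- Including the penalty, the adjusted half-widths become 0.715 × 1.019 = 0.73, 0.649 × 1.019 = 0.66 and 0.535 × 1.019 = 0.55. The conclusion does not change.

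**The case against.** The strongest reply is that nothing here is invalid. Under randomisation the t-test is unbiased, and its standard error already allows for chance imbalance. A reader might infer that pre-existing differences between the arms are being counted as an effect of the psychiatrist. The protocol does not support that: step 3 shows no systematic shift and the nominal error rate. The higher rejection rates apply only to the subset of trials with a large imbalance, and are offset in the rest. This part of the reply stands in full.

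A reader might also object that, with no pre-appointment score, no within-patient response can be calculated. That is not a defect. The comparison is between randomised arms and needs no change score, and an appointment's helpfulness has no prior value.

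The size of the gain is open to challenge. The protocol gives no correlation, the split of the 8 items between helpfulness, confidence and optimism is not stated, and the helpfulness items may relate little to self-efficacy. At ρ = 0.3 the half-width falls by only about 4% before the slope penalty, and about 3% after it. This stands, and is why a range is shown.

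It can also be said that the primary objective is acceptability, that self-efficacy is a secondary objective with its own baseline-adjusted analysis, and that covariates are often left to the statistical analysis plan. The first two explain why the protocol adjusts where the same instrument has a baseline, so the contrast between primary and secondary outcomes is no contradiction. But a covariate need not be the same instrument. As for the third, the protocol does not leave the method open: it names the t-test.

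Last, the protocol is not consistent on whether the Initial Survey precedes randomisation. The Study procedure text randomises after verbal consent, before attendance. Its table lists the survey before randomisation. The Initial Survey section places the survey after the standard appointment. A self-report given once the arm is known would be a weaker covariate. That sets a condition on the fix and does not remove the point.

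**Conclusion.** The point holds as one of efficiency and of robustness to chance imbalance, not of bias. The stated test is valid but sets aside a related baseline score that the trial already collects. With 15 per arm, adjustment would take the 95% half-width from about 0.75 SD to about 0.71, 0.65 or 0.54 SD at correlations of 0.3, 0.5 or 0.7, and would remove on average the part of any chance imbalance in self-efficacy that reaches the estimate. Below about 0.2 nothing is gained, and at most about 2% is lost.

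This rests on the assumed correlations, a roughly linear relation, about 30 analysed participants, and reading the primary outcome as the questionnaire given after the clinic appointment. The statement that the t-test is unbiased also requires the analysed arms to be the arms as randomised. The exclusion of consenting participants without follow-up data, and the removal of withdrawn participants' data, could disturb that. Baseline adjustment would not repair it.

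**What to change.** In the Statistical analysis section, replace the t-test with a prespecified linear model of the Post Appointment Questionnaire average on arm, with the Initial Survey General Self Efficacy score as covariate. Report the adjusted mean difference with its 95% confidence interval.

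State that this score is to be completed before the participant's arm is disclosed and before the psychiatrist is seen, and align the Study procedure text, its table and the Initial Survey section with that order.

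The analysis change costs one sentence and one degree of freedom, with no new patients, visits or instruments. If the arm is currently disclosed before attendance, the survey or the disclosure has to move. Asking the confidence and optimism items before the appointment as well would be optional and is not needed for this fix.

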With the current evidence base for PICS being scarce internationally, and available evidence demonstrating that current interventions are not effective longer-term; further research into prevention, early diagnosis and intervention of this syndrome is considered internationally as a priority [14]. Many post-ICU clinics review patients sometime after discharge, but to our knowledge the effect of an early psychiatric intervention soon after ICU discharge on PICS outcomes has not been investigated. This is despite a recent meta-analysis demonstrating benefit from early psychological intervention targeted to symptomatic individuals following recent trauma[15] and a recent overview of PICS emphasising the importance of early screening and treatment of psychological morbidity to prevent longer term psychological impairment, and suggesting that future research in post-ICU clinics needs to find ways for a more targeted approach to intervention delivery[16].

We hypothesise that an early psychiatric intervention involving evaluation, initial treatment (such as psychoeducation and pharmacotherapy), and referral is feasible and practicable to implement in a post-ICU clinic and acceptable to that patient population Such an intervention may contribute to an improved sense of self-efficacy, improved access of ongoing therapy, and a subsequent reduction in the long-term burden of PICS – both for the individual patients needing this care, and on broader health systems.

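### The only analysis stated for the primary outcome compares visit ratings between arms, so it does not say how acceptable the psychiatric intervention is to those offered it

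*Protocol*

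**What the plan says.** All references are to the Protocol.

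- **Aims and objectives.** The primary objective is "To evaluate feasibility (cost and practicability) and acceptability of an early psychiatric intervention in a post-ICU clinic".
- **Background and rationale.** The hypothesis is that the intervention "is feasible and practicable to implement in a post-ICU clinic and acceptable to that patient population".
- **Post Appointment Questionnaire.** The instrument for the primary outcome "is an 8 item self-reported acceptability measure that has been specifically developed for this study". On content: "Questions focus on whether the participant found their appointment helpful, how confident they feel about managing any psychological symptoms they have or may develop", followed by optimism about recovery. This description does not mention the psychiatrist. The items themselves are in an appendix that is not shown.
- **Statistical analysis.** "Responses to the Post Appointment Questionnaire will be assumed to be additive and averaged to produce the primary outcome measure". The next sentence is the whole of the stated analysis: "Differences between groups will be assessed using t-test". Counts of patients approached, consented, dropped out and died are to be tabulated, with no criterion attached.
- **Sampling and recruitment.** "participants randomised to the control arm will receive standard clinic cares only". Under Early Psychiatric Assessment and Referral Intervention, the other arm has the same usual care and then sees the psychiatrist.
- **Follow-up Survey.** The questionnaire is given again at 6 months. The Statistical analysis section does not say which administration is primary.

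**The concern.** The objective and the hypothesis ask about a level: how acceptable the intervention is to the people offered it. The stated analysis asks about a difference: whether visits with a psychiatrist are rated differently from visits without one. A control participant has not met the psychiatrist, so a control score carries no direct information on whether seeing one is acceptable.

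If the trial is reported as written, its headline is a p-value for relative rating. A well-received intervention added to an already well-liked clinic would appear as no difference. A poorly rated one would appear as a significant benefit if the usual visit was rated lower still. A pilot meant to inform later work would then finish without a stated answer to its own primary question.

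**Working it through.** **Inputs.** The Protocol gives about 30 patients, 15 per arm (Participants and sample calculation). It gives no rating scale, SD, alpha, sidedness or acceptable level, and no basis for the sample size, so there is no figure of the plan's own to reproduce. I assume a two-sided 5% level. For illustration I assume a 1–5 scale and a common SD of 0.8, with 0.6 to 1.2 as the range.

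**Step 1: what the statistic responds to.** With n per arm, t = (mean_I − mean_C) / (SD × √(2/n)). Only the difference enters. Adding the same amount to both means leaves t unchanged.

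- Means 4.2 v 4.2: t = 0, p = 1.
- Means 2.2 v 2.2: t = 0, p = 1.

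This holds for any scale and any SD. By contrast, the intervention-arm mean with its interval, mean ± 2.145 × 0.8/√15 = mean ± 0.44, separates the two cases: 4.2 (3.8 to 4.6) against 2.2 (1.8 to 2.6).

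**Step 2: unequal means.** The standard error is 0.8 × √(2/15) = 0.292.

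| Intervention v control | t | p | Intervention-arm 95% CI |
|---|---|---|---|
| 4.4 v 4.5 | −0.1/0.292 = −0.34 | 0.73 | 3.96 to 4.84 |
| 2.8 v 2.0 | 0.8/0.292 = 2.74 | 0.011 | 2.36 to 3.24 |

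The first row is a highly rated intervention with a null test. The second is a significant test with an intervention mean below the scale midpoint of 3, although its interval includes 3.

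Over the SD range:

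- SD 0.6: standard error 0.6 × 0.365 = 0.219, so t is −0.46 and 3.65.
- SD 1.2: standard error 1.2 × 0.365 = 0.438, so t is −0.23 and 1.83.

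Against the critical value 2.048 (28 df), the second example is significant at SD 0.6 and 0.8 but not at 1.2. These rows are illustrations. The argument rests on Step 1.

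**Step 3: precision of the two estimates** (95% half-widths, no dropout).

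- Intervention-arm mean: 2.145/√15 = 0.55 SD. For SD 0.6, 0.8 and 1.2 this is 0.33, 0.44 and 0.66 points.
- Between-arm difference: 2.048 × √(2/15) = 0.75 SD, or 0.45, 0.60 and 0.90 points.
- With 12 per arm these become 0.64 and 0.85 SD; with 10 per arm, 0.72 and 0.94 SD.

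**Step 4: context only.** With 15 per arm the t-test has 26% power for a 0.5 SD difference and reaches 80% only at 1.06 SD. A null result is therefore likely unless the psychiatrist changes ratings a great deal. That is a matter of pilot size and is not the fault raised here.

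**The case against.** The strongest reply is that the design is add-on. Both arms have the same clinic visit, and one then sees the psychiatrist, so the randomised contrast isolates the added component. For the items on confidence and optimism, an uncontrolled mean cannot separate the psychiatrist's contribution from the usual visit or from the patient's own outlook; the comparison can. This stands, and it is why the difference should stay in the report with its interval.

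Three stronger readings are tempting, and the Protocol does not support them.

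- *The trial cannot show acceptability at all.* The intervention-arm mean can be calculated from the same scores, and consent and dropout counts are tabulated. What is missing is a statement that the within-arm estimate is the result. An unseen statistical analysis plan may add such a summary, but the Protocol itself names only the t-test.
- *The intervention passes or fails on the p-value.* The Protocol nowhere equates significance with acceptability. The point is that it offers no other reading of the primary outcome.
- *Disappointed controls will bias the comparison.* Participants are told about the psychiatric review and controls do not receive it, so this is possible. The Protocol gives no evidence that it happens or how large it would be.

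Also, because the items are not shown, one that names the psychiatrist cannot be ruled out. Controls still could not rate someone they had not seen, so the mismatch would remain, but the extra questionnaire instruction might be unnecessary.

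**Conclusion.** The point holds as a mismatch between the acceptability objective and the one analysis stated for it. Followed as written, the plan yields a relative rating of two visits and no stated level of acceptability. The core argument needs no assumption about scale or SD, since the t statistic is the same for any pair of equal means. The examples with unequal means do rest on an assumed 1–5 scale and SD, and one of them loses significance at the upper end of the SD range.

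A reader might infer that the control arm or the comparison is itself a mistake. It is not: it estimates what the psychiatrist adds. This is a cheap improvement to wording and emphasis that lets the trial answer its own question. It does not show that the design is unsound.

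**What to change.** In Statistical analysis:

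1. State that the acceptability result is the intervention-arm mean Post Appointment Questionnaire score at the clinic-appointment administration, with its 95% CI.
2. Fix the level against which it will be read before any questionnaire responses are seen. Clinic staff cannot be blinded to when the intervention is available, so a later date would allow the level to be chosen with responses in view.
3. Report beside it the between-arm difference with its 95% CI, as the estimate of what the psychiatrist adds to the rating of the visit.

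In Post Appointment Questionnaire, if the form does not already do so, add a line asking intervention-arm participants to rate the psychiatrist appointment itself.

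**Cost.** Protocol wording and at most one line on a form; no extra patients or visits and no change to the control arm. The headline result would carry no p-value. With 15 patients and no dropout, an interval of about ±0.55 SD may straddle the set level and leave the answer open. A proportion would not escape this: 13 of 15 favourable (87%) has an exact 95% CI of 60% to 98%. One primary summary, the mean, is therefore enough.
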